# 1. TRIAL SUMMARY

| Title | A prospective, multicenter controlled trial of heterologous sequential vaccination against COVID-19 in the elderly |
| --- | --- |
| Primary registry and trial identifying number | ClinicalTrials.gov NCT05012800 |
| Secondary identifying numbers | KY-2021-7-7-2 |
| Sources of monetary or material support | The Emergency Key Program of Guangzhou Laboratory |
| Primary sponsor | The Fifth Medical Center of Chinese PLA General Hospital |
| Central contact | Principal Investigator: [name], Ph.D.  [name] [[contact]](mailto:[contact])  Investigator and coordinator: [name], Ph.D.  [name] [[contact]](mailto:[contact])  Study Sites:  Hunyuan County People's Hospital, Datong 037499, Shanxi Province, China  Contact: [name], Ph.D.  The Fifth Medical Center of Chinese PLA General Hospital, Beijing 100039, China  Contact: [name], Ph.D. |
| Study officials/Investigators | Study Principal Investigator  [name], Ph.D.  The Fifth Medical Center of Chinese PLA General Hospital |
| Brief title | Heterologous sequential vaccination against COVID-19 in the elderly |
| Countries of recruitment | P. R. China |
| Condition(s) or focus of study | COVID-19 vaccination |
| Interventions | Two doses of inactivated BBIBP-CorV vaccines and a 3^rd^ dose of recombinant protein ZF2001 vaccine booster. |
| Key eligibility criteria | **Inclusion criteria**   1. Signed informed consent; 2. In females, the urine pregnancy test was negative; 3. At least 6 months of follow-up was completed; 4. HBsAg, anti-HCV, HIV, treponema pallidum hemagglutination assay (TPHA) screening was negative; 5. Armpit temperature was ≤37.0℃; 6. The young group was aged 18–59 years, and the elderly group between 60–80 years.   **Exclusion criteria**   1. In females, the urine pregnancy test positive; 2. Pregnant or lactating women; 3. Known allergies to certain components of these two vaccines; 4. Patients with serious chronic diseases or advanced diseases such as high blood pressure, diabetes, asthma, thyroid disease, *etc*. which cannot be controlled by drugs; 5. Those suffering from thrombocytopenia, hemorrhagic disease or thrombotic disease; 6. Those with congenital or acquired angioedema/neuroedema; 7. Those with a history or family history of convulsions, epilepsy, encephalopathy, other progressive neurological diseases, and psychiatric disorders; 8. Lymphadenopathy； 9. Lymphoma, leukemia and other systemic malignancies; 10. Autoimmune disease; 11. Chronic diseases with cute exacerbation or acute infectious diseases and fever. |
| Study design | Study type: Prospective real-world interventional trial  Allocation: Open, non-randomized  Intervention model: Parallel group  Primary purpose: Prevention |
| Date of enrolment | July 1, 2021 |
| Target sample size | 300 (200 in the elderly group, 100 in the young group) |
| Recruitment status | Recruited |
| Primary outcomes | **Primary endpoint measures**   - Safety profiles within one month after each vaccination dose, including:   1. The incidence of adverse events;   2. Liver function;   3. Kidney function;   4. Blood glucose;   5. Blood lipids. - The definition and grade of adverse events (AEs) were evaluated according to the Common Terminology Criteria for Adverse Events (CTCAE), version 5.0:  1. Grade 1 (mild) - asymptomatic or mild symptoms, clinical or diagnostic observations only, intervention not indicated; 2. Grade 2 (moderate) - minimal, local, or non-invasive intervention indicated, limiting age-appropriate instrumental activities of daily living (ADL); 3. Grade 3 (severe or medically significant but not immediately life-threatening) - indication for hospitalization or prolongation of hospitalization, disabling and limiting self-care ADL. |
| Secondary outcomes | **Secondary endpoint measures**   - Immune protection of the participants:   - - The titers of neutralizing and anti-receptor binding domain (RBD) antibodies at the baseline and the 1^st^, 2^nd^, 4^th^, 7^th^, 8^th^, 10^th^, 13^th^, and 16^th^ months after the first vaccination in each study group. |

# 2. INTRODUCTION

## 2.1. Background

Coronavirus disease 2019 (COVID-19), an emergent acute respiratory infectious disease, has caused unprecedented morbidity and mortality during the pandemic^[1-2]^. Current drug treatment options are limited, making the establishment of an immune barrier through safe and effective vaccination a crucial strategy to control the virus’s spread^[3-4]^. The focus of vaccine research and development is on preventing antibody-mediated infection enhancement and vaccine-enhanced disease. Globally, 83 vaccines are undergoing clinical trials, with 184 vaccine candidates in preclinical evaluation^[5]^. Five technical routes for vaccine development are being pursued in China: inactivated, adenovirus vectors, recombinant subunits, nucleic acids, and attenuated influenza virus vectors. Five novel coronavirus vaccines have been conditionally marketed for emergency use^[6]^. Considering the “safety of the vaccine itself,” the Chinese Center for Disease Control and Prevention’s Novel Coronavirus Vaccine Working Group has drafted “Technical Guidelines for Novel Coronavirus Vaccination,” which outlines 31 conditions for vaccination. According to the National Health Commission, as of June 29, 2022, China has received over 1.2 billion doses of the COVID-19 vaccine, aiming to vaccinate at least 70% of the target population by the end of 2022, gradually establishing a herd immunity barrier.

Clinical research has demonstrated that the severity of COVID-19 is largely determined by the age of the patient, with individuals aged 65 years or older constituting 80% of hospitalizations and facing a 23-fold higher risk of death compared to those under 65^[7]^. This indicates that the elderly are at a high risk of severe disease following COVID-19 infection and have a poor clinical prognosis^[7]^. Considering the current demographic trends in China, priority should be given to vaccinating the elderly to protect them and reduce the risk of COVID-19 infection. However, the majority of available vaccine data are derived from studies involving young and middle-aged healthy individuals, with many phase II COVID-19 vaccine trials seeing limited participation from the elderly^[8-10]^. Although phase III trials consciously enrolled the elderly, individuals with comorbidities and frailty were excluded, resulting in insufficient research data on COVID-19 vaccination in the elderly^[11-12]^. In this context, this study focuses on investigating the safety and effectiveness of COVID-19 vaccination in the elderly, as well as its potential immune mechanisms. The research findings aim to provide theoretical support for the establishment of expert consensus on COVID-19 vaccination of the elderly in China.

## 2.2. Objectives

The aim of this study is to evaluate the safety and immunogenicity of the COVID-19 vaccine in the elderly aged 60–80 years.

## 2.3. Trial design

This trial is investigator-initiated and adheres to the principles of good clinical practice. It is a multi-center, prospective, single-arm clinical study. The trial will include two participant groups: an elderly group aged 60 to 80 years and a younger control group aged 18 to 59 years.

# 3. METHODS

## 3.1. Study setting

This trial will be conducted in two hospitals: the Hunyuan County People's Hospital, Datong 037499, Shanxi Province, China; and the Fifth Medical Center of Chinese PLA General Hospital, Beijing 100039, China.

## 3.2. Eligibility criteria

### 3.2.1. Inclusion criteria

1. Signed informed consent;
2. In females, the urine pregnancy test was negative;
3. At least 6 months of follow-up was completed;
4. HBsAg, anti-HCV, HIV, treponema pallidum hemagglutination assay (TPHA) screening was negative;
5. Armpit temperature was ≤37.0℃;
6. The young group was aged 18–59 years, and the elderly group between 60–80 years.

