### 3.3.2. Intervention assignment

Both the experimental and control groups will receive two doses of the inactivated COVID-19 vaccine, administered on day 0 (baseline) and day 25±3. A third booster dose will be given 6 months after the second dose.

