### 3.3.3. Exit Criteria

The participants may exit the study for any of the following reasons:

1. Voluntarily withdrawal (due to withdrawal of informed consent, loss of informed consent capacity, lack of efficacy, intolerance, adverse events [AEs], etc.);
2. Poor compliance, inability to receive the vaccine as scheduled, or complete the study protocol;
3. Becoming pregnant or lactating during the treatment period;
4. Experiencing complications, AEs, serious AEs (SAEs), or special physiological changes occurring during vaccination that lead the investigator to judge further vaccination as unsuitable;
5. Any other condition deemed by the investigator as necessitating withdrawal from the study.

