## 3.4. Outcomes

### 3.4.1 Primary endpoint measures

- Safety profiles within one month after each vaccination dose, including:

1. The incidence of adverse events;
2. Liver function;
3. Kidney function;
4. Blood glucose;
5. Blood lipids;

- The definition and grade of AEs were evaluated according to the Common Terminology Criteria for Adverse Events, version 5.0:

1. Grade 1 (mild) - asymptomatic or mild symptoms, clinical or diagnostic observations only, intervention not indicated;
2. Grade 2 (moderate) - minimal, local, or non-invasive intervention indicated, limiting age-appropriate instrumental activities of daily living (ADL);
3. Grade 3 (severe or medically significant but not immediately life-threatening) - indication for hospitalization or prolongation of hospitalization, disabling and limiting self-care ADL.

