## 3.5. Participant timeline

Figure 1. The schedule of enrolment, interventions, and assessments.

| **Visits** | **Screening** | **V1** | **V2** | **V3** | **V4** | **V5** | **V6** | **V7** | **V8** | **V9** |
| --- | --- | --- | --- | --- | --- | --- | --- | --- | --- | --- |
| **Timepoint (month)** | **Day**  **-21~0** | **Day 0** | **1^st^** | **2^nd^** | **4^th^** | **7^th^** | **8^th^** | **10^th^** | **13^th^** | **16^th^** |
| **Time window (day)** |  | **± 3** | **± 3** | **± 15** | **± 15** | **± 3** | **± 15** | **± 15** | **± 15** | **± 15** |
| **ENROLMENT:** | | | | | | | | | | |
| Informed consent | × |  |  |  |  |  |  |  |  |  |
| Eligibility screen | × |  |  |  |  |  |  |  |  |  |
| Demographical characteristics | × |  |  |  |  |  |  |  |  |  |
| Medical history | × |  |  |  |  |  |  |  |  |  |
| Urine pregnancy test  (reproductive women) | × |  | × | × | × | × | × | × | × | × |
| Height, weight, blood pressure | × |  |  |  |  |  |  |  |  |  |
| Underarm temperature | × |  |  |  |  |  |  |  |  |  |
| Lab tests & Images*^#^* | × |  |  |  |  |  |  |  |  |  |
| **INTERVENTIONS:** | | | | | | | | | | |
| Allocation |  | × |  |  |  |  |  |  |  |  |
| Vaccination |  | × | × |  |  | × |  |  |  |  |
| 30 minutes’ observing |  | × | × |  |  | × |  |  |  |  |
| **ASSESSMENTS:** | | | | | | | | | | |
| Lab tests*** | × |  | × | × | × | × | × | × | × | × |
| Distribute/recycle diary cards |  | × | × | × | × | × | × | × | × | × |
| Safety (AEs) |  | × | × | × | × | × | × | × | × | × |
| Safety (SAEs) |  | × | × | × | × | × | × | × | × | × |
| Concomitant care |  | × | × | × | × | × | × | × | × | × |
| Humoral immunoassays |  | × | × | × | × | × | × | × | × | × |

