## 3.10. Statistical consideration

### 3.10.1. Analysis of population and missing data

**Full Analysis Set (FAS):** According to the intention-to-treat (ITT) principle, this study aims to include as many participants as possible. Participants who did not complete all three doses of vaccination will be excluded.

**Per-Protocol Set (PPS):** Based on the FAS population, participants with poor compliance will be excluded. Specifically, this set excludes individuals who participated in follow-up no more than six times.

**Safety Set (SS):** Participants with at least one vaccination record and measured AEs/SAEs correspondingly.

**Missing Data Processing:** The missing data on demographic information, safety indicators, and immunogenicity indicators for the FAS and PPS populations will not be imputed.

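### Inclusion criterion 3 requires six months of completed follow-up, which cannot be known at screening and conflicts with the Safety Set; applied in retrospect, it could understate adverse events after doses 1 and 2

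*Protocol*

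**What the plan says.** Criterion 3 reads "At least 6 months of follow-up was completed". It stands in section 3.2.1 and again in the eligibility row of the trial summary (section 1). Neither place says when the six months begin.

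Four other parts of the protocol bear on it:

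- **Schedule (section 3.5).** The row "Eligibility screen" is marked only in the screening column, Day -21 to 0. Dose 1 follows at V1.
- **Exit criteria (section 3.3.3).** Participants may leave through "Voluntarily withdrawal (due to withdrawal of informed consent, loss of informed consent capacity, lack of efficacy, intolerance, adverse events [AEs], etc". The investigator may also end participation for "Experiencing complications, AEs, serious AEs (SAEs), or special physiological changes occurring during vaccination that lead the investigator to judge further vaccination as unsuitable".
- **Primary endpoint and dosing (sections 3.4.1 and 3.3.2).** The endpoint is introduced as "Safety profiles within one month after each vaccination dose, including" adverse events and four groups of laboratory tests. The first two doses are "administered on day 0 (baseline) and day 25±3". For the third: "A third booster dose will be given 6 months after the second dose".
- **Safety Set (section 3.10.1).** It is defined as "Participants with at least one vaccination record and measured AEs/SAEs correspondingly". Section 3.10.2 assigns the primary analysis to this set.

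**The concern.** An inclusion criterion should be decidable when a person enters. This one depends on what happens over the following six months, so it can only be applied looking back. Read literally, it makes ineligible anyone who was vaccinated and then left before six months, and AEs are among the listed reasons for leaving.

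The primary endpoint is safety in the month after each dose. If membership of the trial is conditional on staying six months, the people whose early experience was worst are the likeliest to be missing from the tables meant to show it. The comparison between elderly and younger participants would also be affected if early exit differs by age. The revision history (section 7.1) makes early exit a practical matter: it records that elderly participants dislike frequent blood sampling and become less willing to return.

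**Working it through.** The protocol states no figure that depends on criterion 3. The target of 300 (200 + 100, ratio 2:1) comes without power, AE or dropout assumptions, so there is nothing to reproduce beyond that sum. The check is one of timing, then of set membership, then of possible size.

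**1. Timing of the safety windows**

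- Dose 1 is on day 0, so its one-month window closes at about day 30.
- Dose 2 is on day 25 ± 3, that is day 22 to 28. Adding about 30 days, its window closes at about day 52 to 58.
- Dose 3 comes six months after dose 2, at about month 7 (V5 in the schedule).

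Both early windows therefore close by about month 2. If the six months run from dose 1, anyone who receives dose 3 on schedule has already passed the mark, and the criterion acts directly only on the dose 1 and dose 2 windows.

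**2. Which analysis sets it can change**

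| Set | Own rule (section 3.10) | Effect of criterion 3, counted from dose 1 |
| --- | --- | --- |
| Full Analysis Set | three doses needed, so about month 7 is reached | almost none |
| Per-Protocol Set, breakthrough and pseudovirus analyses | drawn from the Full Analysis Set | almost none |
| Safety Set | one recorded dose with AE data | removes early leavers, if applied |

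On that reading, the only set whose membership criterion 3 could materially change is the one that carries the primary analysis.

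**3. Possible size if it is applied**

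Let p be the AE risk in those who complete six months, d the share of dosed people who leave earlier, and RR the AE risk of leavers relative to completers. All three are assumptions.

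- Incidence in all dosed = (1 − d)·p + d·RR·p
- Incidence in completers only = p
- Understatement = d·p·(RR − 1)

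| p | d | RR | All dosed | Completers only | Understatement |
| --- | --- | --- | --- | --- | --- |
| any | any | 1 | p | p | 0 |
| 5% | 5% | 2 | 0.95 × 5% + 0.05 × 10% = 5.25% | 5.0% | 0.25 points |
| 10% | 10% | 3 | 0.90 × 10% + 0.10 × 30% = 12.0% | 10.0% | 2.0 points |
| 20% | 20% | 3 | 0.80 × 20% + 0.20 × 60% = 28.0% | 20.0% | 8.0 points |

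The third row is a relative understatement of 2.0/12.0 = 17%. Over d from 5% to 20%, p from 5% to 20% and RR from 1 to 3, the range is 0 to 8 points.

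**4. Effect on the comparison between age groups**

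Take p = 10% and RR = 3 in both groups, with 15% of the elderly and 5% of the younger group leaving early (assumptions).

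- Elderly, all dosed: 0.85 × 10% + 0.15 × 30% = 13.0%
- Younger, all dosed: 0.95 × 10% + 0.05 × 30% = 11.0%

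The 2.0-point difference disappears among completers, where both groups show 10.0%.

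**The case against.** The strongest reply is that the Safety Set already settles the matter. It carries the primary analysis and asks for one dose with AE data. It has no follow-up minimum, and nothing in the protocol says that a dosed person who fails criterion 3 is removed from it. A one-dose threshold would have little purpose if everyone in the set had to stay six months, since such people would normally have had both early doses. Short follow-up is dealt with elsewhere, in the Full Analysis and Per-Protocol Sets. Other inclusion criteria are also written in the past tense, so criterion 3 may simply be a badly worded requirement that people be able to complete follow-up.

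Much of this stands. A reader might infer that the primary safety result is biased toward looking safe; the protocol does not support that, because the bias needs criterion 3 to override the Safety Set and no text says it does. Nor does the protocol report that anyone was removed.

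A reader might also reason that the bias equals the whole early-exit rate: if 6 of 200 elderly (an assumed number) left because of an AE, the rate of such AEs would fall from 3.0% to 0 of 194. But that counts AEs that lead to exit, which become zero by construction once leavers are removed. The primary endpoint is the incidence of AEs, where the loss depends on how many leave and on their excess risk.

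What the reply does not remove is the conflict. The Safety Set definition does not say that it applies whatever the eligibility or length of follow-up, and eligibility ordinarily decides who is a participant before analysis sets are formed. The benign meaning of criterion 3 is a guess about intent.

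**Conclusion.** The point holds as an internal contradiction with a conditional consequence. Criterion 3 cannot be assessed at the only time eligibility is checked, and it is at odds with the exit criteria and the Safety Set. The protocol leaves open which text governs a dosed person who leaves before six months.

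If criterion 3 is applied in retrospect and leavers have more AEs than stayers, incidence in the dose 1 and dose 2 windows is understated: by 2.0 points in the central example and by 0 to 8 points over the assumed range. If the Safety Set governs, or leavers have no excess AE risk, the bias from this criterion is zero. The protocol cannot narrow the range, because it gives neither dropout nor AE rates. Confining the effect to doses 1 and 2 assumes that the six months are counted from dose 1, which is not stated.

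**What to change.** 1. Delete criterion 3 in sections 1 and 3.2.1. If it was meant as a condition at enrolment, reword it as willingness and ability to attend the follow-up visits.
2. State in section 3.10.1 that the Safety Set includes everyone who received at least one dose, regardless of length of follow-up, and that the denominator for each dose is the number who received that dose.
3. Check whether any dosed participant was removed under this criterion. If so, include them in the safety tables.

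The cost is a wording change and a check of existing records; the target of 300 is unaffected. The downside is that AE rates may look slightly less favourable if leavers were removed and have to be included again.

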### 3.2.2. Exclusion criteria

1. In females, the urine pregnancy test positive;
2. Pregnant or lactating women;
3. Known allergies to certain components of these two vaccines;
4. Patients with serious chronic diseases or advanced diseases such as high blood pressure, diabetes, asthma, thyroid disease, etc. which cannot be controlled by drugs;
5. Those suffering from thrombocytopenia, hemorrhagic disease or thrombotic disease;
6. Those with congenital or acquired angioedema/neuroedema;
7. Those with a history or family history of convulsions, epilepsy, encephalopathy, other progressive neurological diseases, and psychiatric disorders;
8. Lymphadenopathy；
9. Lymphoma, leukemia and other systemic malignancies;
10. Autoimmune disease;
11. Chronic diseases with cute exacerbation or acute infectious diseases and fever.

## 3.3. Interventions

### 3.3.1. Investigational vaccine product

In this study, the first two doses were China's Sinopharm COVID-19 inactivated vaccine BBIBP-CorV (Vero cells) containing 4 μg per 0.5 mL in a vial. The third booster dose was Zhifei Longcom recombinant COVID-19 vaccine ZF2001 (CHO cells) containing 25 μg per 0.5 mL in a vial. Both vaccines were adjuvanted by aluminum hydroxide. All the participants received the vaccine intramuscularly through a deltoid.

### 3.3.2. Intervention assignment

Both the experimental and control groups will receive two doses of the inactivated COVID-19 vaccine, administered on day 0 (baseline) and day 25±3. A third booster dose will be given 6 months after the second dose.

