**Primary analysis:**

The main endpoint of this study is the safety after vaccination, which involves the evaluation of AEs, SAEs, and laboratory test indices, and performed on the SS.

The AEs/SAEs occurring in the two groups within one month after each dose of vaccination will be statistically described as a categorical variable, and Pearson’s chi-square test or Fisher’s exact test will be used for intergroup comparisons. The AEs/SAEs of the different categories will be summarized in percentages. The laboratory test indices at each follow-up point will be statistically described as continuous variables, and the Mann–Whitney U test will be used for intergroup comparisons. The median values of the laboratory test indices for the two groups will be calculated at each follow-up point, as well as the corresponding intergroup differences and 95% CIs.

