## 3.11. Safety/harms

AEs and SAEs will be monitored and recorded from the time the participant signed the informed consent form to the completion of the follow-ups. AEs/SAEs will be recorded in detail, including onset date, duration, severity, treatment, and relation to the investigational medical product. All AEs/SAEs will be followed up until finalized (recovery/relief, stability, death, or other explainable circumstances, such as lost to follow-up).

Once identified, SAEs must be acted upon and reported within 24 hours. They will be reported to the Institutional Review Board (IRB) as soon as possible.

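### Dose 2 is due 2–8 days before the one-month dose-1 AE period ends (30-day month), and section 3.3.2 and Figure 1 give it different windows

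*Protocol*

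**What the plan says.** Dosing: section 3.3.2 gives both age groups two inactivated doses "administered on day 0 (baseline) and day 25±3", with the booster six months after the second. Figure 1 (section 3.5) marks vaccination at V1 (day 0), V2 (1st month, ±3 days) and V5 (7th month, ±3 days), so dose 2 belongs to V2.

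Endpoint: section 3.4.1 sets the primary endpoint as "Safety profiles within one month after each vaccination dose", with AE incidence as its first item; the trial summary repeats this. The primary analysis in section 3.10.2 says "The AEs/SAEs occurring in the two groups within one month after each dose of vaccination will be statistically described as a categorical variable", with a chi-square or Fisher's exact test between age groups. A month is not defined in days, and neither section ends the dose-1 period when dose 2 is given.

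Attribution: under section 3.11, "AEs/SAEs will be recorded in detail, including onset date, duration, severity, treatment, and relation to the investigational medical product". Section 3.3.1 states that "the first two doses were China's Sinopharm COVID-19 inactivated vaccine BBIBP-CorV", so doses 1 and 2 are the same product.

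**The concern.** Two things are fixed in ways that do not fit together.

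First, the protocol carries two windows for one injection. With a 30-day month, a participant dosed on day 24 is on schedule under 3.3.2 and early under Figure 1; one dosed on day 31 is on schedule under Figure 1 and late under 3.3.2. This has a practical side, because section 3.3.3 lists failure to be vaccinated on schedule among the reasons for leaving the study.

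Second, an interval of about 25 days between doses is shorter than a one-month safety period. The first days after dose 2 then lie within one month of both doses. A reaction to dose 2 with onset in those days meets the stated definition of a dose-1 event as well. The recorded relation to the product cannot separate the two doses, because the product is the same; the onset date can.

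At stake is the per-dose reading of the first item of the primary endpoint. A dose-2 reaction counted under dose 1 raises the dose-1 incidence, and an age difference that arises after dose 2 can appear in the dose-1 comparison.

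**Working it through.** The protocol states no overlap figure, so there is none to reproduce. The check is date arithmetic.

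**Inputs.** Dose 1 on day 0; dose 2 on day d, with d = 22 to 28 (3.3.2). Figure 1 window for dose 2: M − 3 to M + 3, where M is the length of a month in days. AE period: M days after each dose (3.4.1, 3.10.2). M is not given, so 28, 30 and 31 are tried.

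**Step 1: do the dosing windows agree?** Intersect days 22–28 with M − 3 to M + 3.

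**Step 2: how far does the dose-1 period run past dose 2?** Overlap = max(0, M − d). For M = 30: 30 − 22 = 8, 30 − 25 = 5, 30 − 28 = 2.

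| M (days) | Figure 1 window | Days in both windows | Overlap under 3.3.2, d = 22 / 25 / 28 | Overlap under Figure 1 |
| --- | --- | --- | --- | --- |
| 28 | 25–31 | 25–28 (4 of 7) | 6 / 3 / 0 days | 0–3 days |
| 30 | 27–33 | 27–28 (2 of 7) | 8 / 5 / 2 days | 0–3 days |
| 31 | 28–34 | 28 (1 of 7) | 9 / 6 / 3 days | 0–3 days |

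The two windows coincide only if M = 25, which is not a month. Under 3.3.2 the overlap vanishes only with a 28-day month and dose 2 on day 28.

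**Step 3: what is not affected?** For d up to 30 and a 30-day period, the dose-1 and dose-2 periods together cover day 0 to day d + 30, whether or not the first is cut at dose 2. Incidence after any dose is therefore the same. Dose 3 comes six months after dose 2, so its period overlaps no other. Laboratory indices are analysed by follow-up point.

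**Step 4: can the effect be sized?** Not from the protocol, which gives no AE rates, onset times or within-person correlation. An assumed example shows how little can be said. Take p = 10% reacting after each dose, d = 25, M = 30, and let c be the share of dose-2 reactions falling in the 5 shared days. Then c = 5/30 = 0.167 if onset is uniform over 30 days, and c = (1 − e^−5)/(1 − e^−30) = 0.993 if it is exponential with a mean of 1 day. If shared-day events were counted under both doses, the apparent dose-1 incidence would be:

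- the same people react to both doses: p = 10%, no change;
- independent reactions: 1 − (1 − p)(1 − cp) = 11.5% to 18.9%;
- different people react: p + cp = 11.7% to 19.9%.

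The answer runs from nothing to almost double, depending entirely on assumptions.

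**The case against.** The best reply is that this is a counting rule, and counting rules belong in a statistical analysis plan, which is not at hand. Overlapping periods do harm only if an event in the shared days is tabulated under both doses, and the protocol does not say that it is. Diary cards are handed out or collected at V1 and V2, so the dose-1 card may well come back when dose 2 is given, and onset dates are recorded anyway. Month 1 may also be just a nominal label for the day-25 visit: the booster is six months after dose 2 in 3.3.2 and at month 7 in Figure 1.

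Much of this stands. A reader might infer that the trial double-counts events, or that the dose-1 incidence is nearly doubled. The documents support neither. The first is not stated. The second needs literal double counting, almost all reactions within five days, and no one reacting to both doses, all at assumed rates. Nor is the absence of an attribution rule the point, since such a rule may exist elsewhere.

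What remains is what the protocol itself fixes: a dose-1 period that includes the first days after dose 2, and two windows for that dose which no month of 28 to 31 days reconciles. A nominal label would explain the month-1 heading, but the ±3 days attached to it is still a window in days. Section 3.9 also places discussion of the statistical plan after the step of locking the database. In an open, non-randomised study, that is a reason to write the rule into the protocol.

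**Conclusion.** The point holds as an inconsistency in the dosing window together with a badly fixed primary period. The windows share 2 of 7 days with a 30-day month (4 with 28, 1 with 31). Under 3.3.2 the dose-1 AE period runs 2–8 days past dose 2 (0–6 with 28, 3–9 with 31). These figures rest only on the protocol's windows and the assumed length of a month.

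The consequence is conditional. If AEs are reported per dose and the stated period is applied literally, dose-1 incidence can be raised and the dose-1 comparison between age groups blurred, by an amount that the protocol does not allow one to derive. Both groups follow the same schedule, and recorded onset dates already permit a clean count. Severity is minor to moderate.

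**What to change.** 1. In Figure 1, label V2 as 1st month (day 25±3), and note that the month-1 laboratory and antibody samples are taken at this visit. This restates the nominal sampling time for those measurements, so it should be explicit.
2. In the trial summary (primary outcomes), 3.4.1 and the primary analysis in 3.10.2, add: 'The dose-1 safety period ends at the dose-2 injection. Each AE is assigned to the most recent dose by onset date. The period after doses 2 and 3 is 30 days.'
3. Assign by onset date, not by visit interval. With V2 on days 22–28 and V3 at month 2 ±15 (days 45–75 with 30-day months), the gap between them can be anything from 45 − 28 = 17 to 75 − 22 = 53 days, so a visit interval would not stand in for 30 days.
4. The summary lists participants as recruited, so report the actual day of dose 2 in each age group.

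The cost is one entry and a note in Figure 1, and the same short text in three places. No new data or visits are needed, because 3.11 already records onset dates.

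There are two downsides. The dose-1 period becomes 22–28 days, shorter than those after doses 2 and 3, and must be labelled so wherever the three are shown together. A late reaction to dose 1 with onset after dose 2 will be counted under dose 2.
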